### Trial objectives

#### Primary objectives

The primary objectives of this study are (1) to determine whether the EMBalance DSS is an accurate supportive tool for the diagnosis and management plan of dizziness and/or balance disorders when used by non-specialist doctors and (2) to establish the feasibility of testing the DSS in a large-scale RCT. These objectives will be measured as follows:Percentage of agreement between the diagnosis and management plan established by the non-specialist doctors (using the DSS and not using the DSS) and the gold standard as determined by an overseeing expert and according to current evidence-based guidelines for the diagnosis and/or management of these disorders

The primary outcome assessment criteria are shown in Table 3.

**Table 3 Tab3:** Primary outcome assessment criteria

Diagnosis (Dx)				
Single		Concurrent		
If doctorDx = expert Dx	100 %	If doctorDx_1_ + Dx_2_ = expertDx_1_ + Dx_2_		100 %
If doctorDx ≠ expert Dx	0 %	If doctorDx_1_ + Dx_2_ ≠ expertDx_1_ + Dx_2_		0 %
		If doctorDx_1_ = expertDx_1_ and doctorDx_2_ NA/≠ expertDx_2_		50 %
Management (Mng)				
Single		Multiple		
If doctorMng = expertMng	100 %	Maximum number of correct Mng plans = 2	If doctorMng_1,2_ = expertMng_1, 2_	100 %
If doctorMng ≠ expertMng	0 %		If doctorMng_1,2_ ≠ expertMng_1,2_	0 %
			If doctorMng_1_ = expertMng_1_ and doctorMng_2_ NA/≠ expertMng_2_	50 %
		Maximum number of correct Mng plans = 3	If doctorMng_1,2,3_ = expertMng_1,2,3_	100 %
			If doctorMng_1,2,3_ NA/≠ expertMng_1,2,3_	0 %
			If doctorMng_1_ = expertMng_1_ and doctorMng_2,3_ NA/≠ expertMng_2,3_	33.3 %
			If doctorMng_1,2_ = expertMng_1,2_ and doctorMng_3_ NA/≠ expertMng_3_	66.6 %
		Maximum number of correct Mng plans = 4	If doctorMng_1,2,3,4_ = expertMng_1,2,3,4_	100 %
			If doctorMng_1,2,3,4_ ≠ expertMng_1,2,3,4_	0 %
			If doctorMng_1_ = expertMng_1_ and doctorMng_2,3,4_ NA/≠ expertMng_2,3,4_	25 %
			If doctorMng_1,2_ = expertMng_1,2_ and doctorMng_3,4_ NA/≠ expertMng_3,4_	50 %
			If doctorMng_1,2,3_ = expertMng_1,2,3_ and doctorMng_4_ NA/≠ expertMng_4_	75 %
Diagnosis		100 % = correct		
		50 % = half correct		
		0 % = incorrect		
Management		100 % = fully correct		
		>50 % = majority correct		
		50 % = half correct		
		<50 % = partially correct		
		0 % = incorrect		

These criteria determine the level of agreement between the non-specialist doctor and the overseeing expert

#### Secondary objectives

The following secondary objectives are also being evaluated in the trial:Assessment of the usability of DSS in primary careDetermination of the number of referrals to secondary care needed in both the + DSS and − DSS groupsDetermination of the number and cost of investigations required for an accurate diagnosis by the DSS non-specialist doctor user (+DSS) vs. the non-DSS non-specialist doctor user (−DSS)Effectiveness of treatment proposed by DSS vs. treatment proposed by non-DSS non-specialist doctorAssessment of feasibility factors (participation rate, dropout rate, reason for exclusion from the trial, trial accomplishment with the time frame)

### Sample size

Sample size was not formally calculated, owing to lack of available data with respect to standard deviation. However, 200 participants should provide sufficient power for the analysis. Participants will be equally distributed in the 4 countries; that is, 50 patients will be recruited in each country. Regarding physicians, each country site will collaborate with 2 overseeing experts and 10–15 non-specialist doctors. The number of patients recruited per centre will be determined by the number of non-specialist doctors available at each site. This is because non-specialist doctors are expected to learn from the EMBalance DSS, as the system will guide the doctors through the diagnostic procedures with access to supportive learning material, such as video tutorials on diagnostic manoeuvres. To minimise the contamination effect that this might have on non-specialist doctors’ decisions, each clinician will be expected to see a maximum of six patients.

Competitive enrolment programs will not be implemented. This decision was adopted in accordance with recent evidence which suggests that competitive enrolment practices have not proved a significant effect in study recruitment, while posing ethical dilemmas and compromising the study design [16].

### Recruitment procedures

The recruitment strategy was adjusted to the characteristics of each participating centre. Potential participants will be identified when they contact the research clinic. The staff member who serves as the point of contact will ask the patient whether he or she experiences dizziness or vertigo. A patient who confirms these symptoms will receive a study information leaflet to consider participation.

### Sequence generation

Randomisation sequences have been created for each centre using Research Randomizer v4.0 software [17]. Eligible patients will be randomised in a 1:1 ratio (100 participants in each group). In accordance with the random allocation sequence, a note containing the allocation group will be placed inside an opaque, sealed envelope which will be given to the non-specialist doctor at the time of recruitment.

### Allocation concealment

The allocation sequence will be concealed from the researcher by enrolment of participants via sequentially numbered envelopes. Additionally, a patient identification trial number will be assigned to each envelope, which will permit retrospective monitoring of patient allocation. The research nurse will be instructed to strictly follow this sequence.

### Blinding

The EMBalance trial is a single-blind study. The clinical research nurse responsible for patient recruitment and overseeing experts will be blinded.

### Data collection

Non-specialist doctors and patients will enter the data in bespoke case report forms (CRFs) in paper format, and the CRF data will be transferred into a purpose-built electronic database. CRFs were designed and will be completed with reference to the Joint Unit Guide for the Design, Use and Completion of Paper Case Report Forms. The completion of CRFs will be signed off by the chief investigator (CI) or a delegated authorised individual. A blank hard copy of the CRF was submitted for review by the REC and the sponsor. A copy is also included within the trial master file.

### Statistical analysis

Data analysis will be performed using SPSS version 16.0 software (SPSS, Chicago, IL, USA) and the StatXact statistical software package (Cytel, Cambridge, MA, USA). Statistical significance will be set to 0.05. Descriptive statistics will be calculated and presented. Comparisons which will be made include the following:Proportion of correct diagnosis by specialists to non-specialists and treatments with and without DSS use according to the overseeing expert’s diagnosis and treatmentComparison of the number of laboratory investigations prescribed with and without DSS useComparison of the number of investigation referrals with and without DSS useComparisons of improvement according to the patient at baseline and after 3 months of follow-up, based on the following tool scores: Dizziness Handicap Inventory, EQ-5D-3 L Questionnaire, visual analogue scale scores before and after treatment in the DSS vs. non-DSS user groups

For categorical values (e.g., referral rate), the chi-square test will be used for comparisons between groups. The Bonferroni correction will be used in cases of multiple comparisons. Normality will be tested with the Kolmogorov-Smirnov test. If normality is met, Student’s *t* test will be used. If not, a non-parametric Mann-Whitney *U* test will be used instead. For comparisons before and after treatment, a paired *t* test will be used regarding numeric data (e.g., questionnaire scores) after normality testing.

Because of the close monitoring of all study participants, the proportion of missing data is not expected to be substantial. In the unlikely event that more than 10 % of values corresponding to primary outcome measures are missing, recruitment will be extended to collect additional data.

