## Discussion

The EMBalance project combines the efforts of experts from the fields of bioengineering and medicine to create a tool to support non-specialist doctors in their decision-making. The EMBalance DSS was developed to aid healthcare professionals in primary care while enabling clinicians to undertake the final decision about the management and treatment of the patient. The design of this protocol has been a challenge for the authors due to the need to conceive of a harmonised protocol suitable for all clinical settings (e.g., composition of a non-specialist doctors group). The present document establishes the key requisites to obtain a unified set of data from all participating countries while taking into account the potential benefits derived from both doctors’ and patients’ participation.

From the patient’s perspective, the use of the EMBalance platform is a minimally invasive intervention which is accompanied by multiple advantages: (1) better and earlier diagnosis and treatment for the balance disorder, (2) review of the participant’s case by a renowned expert and (3) improvement of the patient’s quality of life. Despite the support of the EMBalance DSS, however, non-specialist doctors are asked to exercise their clinical judgement, which ultimately will be compared with an expert’s opinion. Although at first glance this could negatively affect doctors’ willingness to participate in the trial, it will benefit their participation by providing guidance for the diagnostic procedure of the ‘dizzy’ patient, access to supporting learning material, and a unique chance to receive feedback from national and international experts in neuro-otology.

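### Most doctors will see patients in both arms and are expected to learn from the DSS, which pulls the comparison towards no difference; the named tests also ignore the randomisation centre and the doctor

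*Protocol article*

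**What the plan says.** All references are to the protocol article.

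- **Who is studied.** Study participants and subject selection calls the non-specialist doctors the primary participants. Primary objectives scores each doctor's diagnosis and plan against the expert's.
- **Allocation.** Sequence generation: "Randomisation sequences have been created for each centre". Allocation is 1:1 by patient, 100 per arm, and the envelope goes to the doctor at recruitment. All non-specialist doctors are trained on the DSS, and none is reserved for the control arm.
- **Doctors.** Each country has 10 to 15: general practitioners in the UK, ENT residents in Belgium and Greece, neurology residents in Germany.
- **Learning.** Sample size: "non-specialist doctors are expected to learn from the EMBalance DSS". The authors call this contamination, and to limit it "each clinician will be expected to see a maximum of six patients".
- **Feedback.** Among the benefits to doctors, the Discussion lists "a unique chance to receive feedback from national and international experts in neuro-otology". It gives no timing.
- **Analysis.** Statistical analysis: "For categorical values (e.g., referral rate), the chi-square test will be used for comparisons between groups". Numeric data get a t test or a Mann-Whitney test, and "Statistical significance will be set to 0.05". No term for centre, doctor or visit order is named.
- **Size.** "Sample size was not formally calculated, owing to lack of available data with respect to standard deviation", followed by "However, 200 participants should provide sufficient power for the analysis".

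**The concern.** The outcome is a doctor's decision, and the same doctor will usually decide with the DSS for some patients and without it for others. Whatever the doctor learns in DSS visits can improve later control decisions. That raises the control rate and moves the estimated DSS effect towards zero. A diluted result could make a useful tool look ineffective, or mis-size the large trial whose feasibility is a primary objective. Since no sample-size calculation is given, no margin is shown that could absorb the loss.

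A separate matter is the analysis. Randomisation is by centre, and centres differ in doctor type, so correct rates may well differ between them. A pooled test leaves that variation in the standard error and gives up power that stratification would recover.

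**Working it through.** There is no power figure to reproduce. The checks below use the protocol's counts plus labelled assumptions: two-sided 0.05 (sidedness is not stated), and a fully correct decision as a yes/no outcome.

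**1. How many doctors see both arms.** 200/60 = 3.3 and 200/40 = 5.0 patients per doctor. With m patients and 1:1 allocation not balanced by doctor, the chance of seeing one arm only is 2 × 0.5^m: 25 %, 12.5 %, 6.3 % and 3.1 % for m = 3, 4, 5, 6. So most doctors see both arms, but not all.

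**2. Exposed controls.** A doctor's k-th patient has no earlier DSS case with probability 0.5^(k−1). The expected share of controls seen after the first DSS case is the mean of 1 − 0.5^(k−1) over k = 1 to m. For m = 3 this is (0 + 0.5 + 0.75)/3 = 42 %. For m = 4, 5, 6 it is 53 %, 61 % and 67 %. Six is the cap, not the average.

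**3. Dilution.** Assume 50 % correct without and 70 % with the DSS, n = 100 per arm. With p̄ the mean of the two rates, power = Φ{[Δ − 1.96√(2p̄(1−p̄)/n)] / √[(p₀(1−p₀) + p₁(1−p₁))/n]}. Without carry-over this is Φ[(0.20 − 0.1358)/0.0678] = 83 %. If exposed controls gain half the effect, Δ = 20 × (1 − 0.5 × share), and the control rate becomes 70 % − Δ:

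| Patients per doctor | Exposed controls | Observed difference (points) | Power |
|---|---|---|---|
| 3 | 42 % | 15.8 | 64 % |
| 4 | 53 % | 14.7 | 58 % |
| 5 | 61 % | 13.9 | 53 % |
| 6 | 67 % | 13.3 | 50 % |

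A simulation (40 doctors × 5 patients, DSS effect 0.9 logit, doctor SD 0.6, centre SD 0.3) agrees. Carry-over of 0/25/50/100 % gives 19.4/16.2/13.0/7.3 points and power of 82/66/48/19 %.

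**4. Ignoring centre.** At assumed control rates of 20/50/60/80 % and no DSS effect, the pooled test rejects 3.4 % of the time and a centre-stratified test 5.2 %. With a DSS effect of about 0.9 logit, power is about 73 % against 80 %; at 1.0 logit it is 82 % against 87 %.

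**5. Ignoring doctor.** With patients randomised within centre, doctor SD up to 0.9 logit and no DSS effect, the unadjusted test rejects 4.1 to 5.5 %. Inflation to 7.6 to 15.1 % appears only if whole doctors are randomised, which is not this design. If the DSS benefit averages zero but varies between doctors with SD 0.8 to 1.2 logit (doctor SD 0.8), rejection is 6.7 to 8.1 %.

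**6. What a model can recover.** With half carry-over and five patients per doctor, adding the number of earlier DSS cases as a main effect leaves the arm effect at about 13.7 points, because the carry-over occurs only in controls. An arm-by-prior-exposure interaction recovers about 20 points, with less precision. It rests on unexposed patients, about 100 × (1 − 0.6125) = 39 per arm. The standard error is √[(0.25 + 0.21)/38.75] = 10.9 points, against √[(0.246 + 0.21)/100] = 6.8 for the diluted comparison. Power for 20 points in that subset is about 43 %.

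**The case against.** The strongest reply has four parts.

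- **The authors saw the problem and capped patients per doctor.** This stands in part: fewer patients per doctor means fewer exposed controls (67 % at six, 42 % at three). A large share remains exposed.
- **This is a feasibility study, and the bias is towards no difference**, so it would not manufacture a benefit. That lowers the severity. Accuracy is nevertheless a stated primary objective, tested at 0.05.
- **Model detail may sit in an analysis plan not shown.** That is possible, but the article names specific unadjusted tests rather than leaving the method open.
- **The size of carry-over is unknown.** This stands: the half share is illustrative.

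A reader might go further and infer three things that the documents do not support. One is that the missing terms cause the dilution; it comes from the design, and a chi-square test with or without a centre or doctor term faces the same contaminated controls. Another is that the error bars are wrong because patients cluster within doctors; individual randomisation leaves the test near nominal or mildly conservative. The inflation in step 5 needs doctor-specific odds ratios spread over about exp(±1.96 × 0.8) = 0.21 to 4.8, or wider, around no average effect, and the protocol gives no variance data. The third is that experts teach doctors between trial patients; feedback is promised, but its timing is not stated.

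**Conclusion.** The point holds in two parts of different kinds. First, the design probably dilutes the DSS effect. The protocol expects the learning, and 42 to 67 % of controls at three to six patients per doctor follow a DSS case by the same doctor. The direction is towards zero if learning improves control decisions. The size cannot be set from the document; at half carry-over it would be 4 to 7 points of a true 20. Second, the named tests discard the randomisation centre. If centre rates differ widely this costs about 7 points of power at the assumed rates, and less if they are similar. The pooled test is then conservative, not anti-conservative. Type I error inflation from DSS benefit varying between doctors depends on assumptions and is secondary. It would matter mainly when generalising to other doctors.

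**What to change.** 1. **Primary analysis.** Use arm and centre as fixed effects and doctor as a random intercept, or a centre-stratified test. Fit a random arm slope by doctor as sensitivity.
2. **Data.** Record doctor ID and the order of each doctor's visits.
3. **Supportive contamination analysis.** Pre-specify either an arm-by-prior-DSS-exposure interaction or a comparison restricted to patients seen before the doctor has completed a DSS case. A main effect of earlier cases alone is not enough. State that this estimate is much less precise. It also does not remove any effect of the DSS training that all doctors receive.
4. **Reporting.** Say that the main estimate is probably diluted, and carry this into the planning of the large trial.
5. **Feedback.** Hold study feedback to a doctor until the diagnosis and plan for that doctor's last trial patient are recorded. This concerns feedback on the doctor's performance, not communication needed for a patient's care.

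The cost is revised analysis wording, two simple fields, a slightly more complex model, an imprecise supportive estimate and later feedback to doctors. Allocation and recruitment do not change.

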## Methods/design

EMBalance is a feasibility and/or proof-of-concept study. It is designed as a non-commercial, international, multi-centre, single-blind, parallel-group randomised controlled trial (RCT) in accordance with the Standard Protocol Items: Recommendations for Interventional Trials (SPIRIT) guidelines [15] (see Additional file 1). The EMBalance study will be carried out simultaneously in the United Kingdom, Germany, Greece and Belgium. Both primary and tertiary care settings will be involved in these four countries. Table 1 provides the names of all participating clinical centres.

**Table 1 Tab1:** Participating centres: a comprehensive list of primary and tertiary care settings in the EMBalance study across Europe

Institution	Primary care setting	Tertiary care setting
Greece (University of Athens)	Hippocrateio Hospital	Hippocrateio Hospital
Belgium (Antwerp University)	Antwerp University Hospital	Antwerp University Hospital
Germany (University of Freiburg)	Freiburg University Medical Centre	Freiburg University Medical Centre
UK (University College London)	Keats Group Practice	National Hospital for Neurology and Neurosurgery
	Hampstead Group Practice	
	Parliament Hill Practice	
	James Wigg Practice	
	Brondesbury Medical Centre	

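### Bonferroni is fixed for multiple comparisons; on the two primary outcomes Holm gives the same family-wise error and never rejects fewer hypotheses

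*Protocol article*

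**What the plan says.** The Statistical analysis section of the protocol article sets one threshold, "Statistical significance will be set to 0.05", and one multiplicity rule, "The Bonferroni correction will be used in cases of multiple comparisons". The rule follows the sentence on chi-square tests for categorical data and precedes the choice between the t test and the Mann-Whitney test. It names no family and no number of tests, and gives no order of priority.

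Under Primary objectives the outcome is a single item, "Percentage of agreement between the diagnosis and management plan established by the non-specialist doctors" compared with the overseeing expert. Table 3, however, scores diagnosis and management separately, which gives two primary comparisons. The Statistical analysis section also lists between-arm comparisons of laboratory investigations, investigation referrals, and "Dizziness Handicap Inventory, EQ-5D-3 L Questionnaire, visual analogue scale scores before and after treatment in the DSS vs. non-DSS user groups". That is five more, so at least seven in all.

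On size, the article says "Sample size was not formally calculated, owing to lack of available data with respect to standard deviation" and then "However, 200 participants should provide sufficient power for the analysis". Allocation is 1:1 with 100 patients per group (Sequence generation). The trial is described this way: "EMBalance is a feasibility and/or proof-of-concept study".

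**The concern.** Defining the family could be left to a statistical analysis plan. The method could not be left open in the same way, because the article fixes it, and a plan that followed the article would have to use Bonferroni.

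For two primaries, Bonferroni requires each p-value to reach 0.025. Holm also requires the smaller p-value to reach 0.025, but then tests the larger at 0.05. The family-wise error bound is the same and no extra assumption or patient is needed. The first primary objective covers both diagnosis and management, so the chance of showing both matters, and that is where Bonferroni loses most. No sample-size calculation shows that there is power to spare.

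The unnamed family is a related weakness. The per-test level could be 0.05/2 = 0.025 or 0.05/7 = 0.0071, and the article does not settle which before results are seen.

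**Working it through.** **Inputs from the article:** significance level 0.05 (sidedness not stated; two-sided assumed), 100 per arm, two primary comparisons, at least five others. The article gives no power, effect size or SD, so there is no stated power to reproduce.

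**Assumptions:** agreement of 50 % vs 70 % on both primaries, with other rates shown below. Each score is treated as a simple proportion and clustering by doctor is ignored.

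**1. Power of one test.** The standardised shift is δ = |p2 − p1| / √(2·p̄(1 − p̄)/n) = 0.20 / √(2 × 0.6 × 0.4 / 100) = 0.20 / 0.0693 = 2.887. Power is Φ(δ − z).
- Level 0.05: Φ(2.887 − 1.960) = 0.823
- Level 0.025: Φ(2.887 − 2.241) = 0.741
- Level 0.00714: Φ(2.887 − 2.690) = 0.578

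With separate variances under the alternative, the usual two-proportion formula gives nearly the same values. The range over assumed rates is:

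| Assumed rates | 0.05 | 0.025 | 0.00714 |
|---|---|---|---|
| 50 vs 60 % | 0.29 | 0.21 | 0.10 |
| 50 vs 65 % | 0.57 | 0.46 | 0.29 |
| 50 vs 70 % | 0.83 | 0.75 | 0.58 |
| 60 vs 80 % | 0.88 | 0.81 | 0.66 |

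At 50 vs 70 %, 80 % power needs 93, 113 and 149 per arm at the three levels.

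**2. Holm against Bonferroni on the two primaries, both effects real, independent tests.** Write a = 0.823 (power at 0.05) and b = 0.741 (power at 0.025).
- Bonferroni, each: b = 0.741. Both: b² = 0.549.
- Holm, each: b + (a − b)·b = 0.741 + 0.082 × 0.741 = 0.802.
- Holm, both: a² − (a − b)² = 0.677 − 0.007 = 0.671.
- At least one, either method: 1 − (1 − b)² = 0.933.

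A simulation of 400,000 draws at correlations 0, 0.3 and 0.6 gives these ranges:

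| Quantity (50 vs 70 % on both) | Bonferroni, 2 tests | Holm, 2 tests |
|---|---|---|
| Power, each primary | 0.74 | 0.79-0.80 |
| Power, both primaries | 0.55-0.62 | 0.67-0.72 |
| At least one | 0.86-0.93 | same |

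At 50 vs 65 % on both, power for each moves from 0.46 to 0.51, and for both from 0.21-0.32 to 0.32-0.41.

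**3. Only one effect real.** Holm gives 0.741 + 0.082 × 0.025 = 0.743 against 0.741, so the gain is negligible.

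**4. Family size.** At 50 vs 70 %, power per primary is about 0.58 with Bonferroni over seven, 0.59 with Holm over the same seven, and 0.74 with Bonferroni over two. Going from seven tests to two is worth about 0.16. Holm on the two then adds 0.05-0.06.

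**5. Error rates, all nulls true, independent tests.**
- Bonferroni over seven: 1 − (1 − 0.00714)⁷ = 0.049.
- The two primaries alone, either method: 1 − 0.975² = 0.049.
- Holm on the primaries, five secondaries each at an unadjusted 0.05: 1 − 0.975² × 0.95⁵ = 1 − 0.951 × 0.774 = 0.264.

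Over correlations 0 to 0.6 the simulated error for that last scheme is 0.18-0.265. If the secondaries are tested by Holm only after both primaries succeed, it is 0.045-0.049. That scheme holds 5 % in general. If either primary null is true, reaching the secondaries already requires a counted false rejection. If neither is true, Holm on the secondaries holds 5 % by itself.

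**The case against.** The strongest case against is that Bonferroni is valid, so nothing in the article is wrong, and that defining the family is normal work for an analysis plan that is not shown. Both statements are true. The unnamed family is therefore not held against this condensed article as an omission. What stands is narrower: the article commits to one method, and another is at least as powerful on whichever family is meant.

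A reader might infer that Bonferroni is applied across all seven or more comparisons, that this pulls primary power down to 58 %, and that Holm on two primaries recovers it at no cost in error. The text does not support that. The rule could equally mean the two primaries, or follow-up comparisons within a multi-category table. Most of the gap between 0.58 and 0.80 comes from the number of tests. The error rate is equal only for the two primaries: a seven-test Bonferroni protects all seven, and leaving five secondaries unadjusted gives that protection up.

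The article also does not say whether success needs both primaries or either one. If both were required, each could be tested at 0.05 with no adjustment, giving 0.823² = 0.677 for both under independence. Holm, at 0.671, comes close to that; Bonferroni, at 0.549, does not. So this point also counts against the sentence as written.

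Finally, the rates are assumed, Table 3 uses graded scores, and each doctor may see up to six patients. These affect the sizes quoted. They do not affect the ranking, because every Holm threshold is at least as large as Bonferroni's on the same p-values.

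**Conclusion.** The point holds as an improvement to a valid method. On any family the sentence may mean, Holm keeps Bonferroni's family-wise error and never rejects fewer hypotheses. For the two primaries at an assumed 50 % vs 70 % and 100 per arm, the gain is 0.05-0.06 in power for each and about 0.10-0.12 for both, provided both effects are real. It is close to zero if only one is, and zero for the chance of at least one rejection. These sizes rest on rates that the article does not give and on ignoring clustering and graded scoring. Whether the trial is short of power cannot be established from the article: at an unadjusted 0.05 the assumed rates give anything from 0.29 to 0.88. In a feasibility or proof-of-concept trial the consequence is modest.

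**What to change.** Replace the Bonferroni sentence with:

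> The two primary comparisons (diagnosis agreement and management agreement) are tested with the Holm procedure at a two-sided family-wise 0.05.

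Then state one of two rules for the secondary comparisons. Either they are exploratory, reported as estimates with unadjusted intervals and no confirmatory claim, or they are tested with Holm only after both primaries succeed, which keeps the overall family-wise error at 5 %. The first gives up any protection that a wider Bonferroni family would have given. The second allows no secondary claim unless both primaries are significant.

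The cost is one or two sentences and no patients. The one technical drawback is that simultaneous confidence intervals matching Holm are less direct than Bonferroni intervals.

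### The comparison of three-month improvement between arms (DHI, EQ-5D-3L, VAS) is tied only to a paired t test, which does not compare arms; no between-arm test is linked to these scores

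*Protocol article*

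**What the plan says.** Under Statistical analysis, the last of the listed comparisons is patient-reported improvement between baseline and three months on the DHI, the EQ-5D-3L and a VAS. It is framed as a contrast of arms: "visual analogue scale scores before and after treatment in the DSS vs. non-DSS user groups". It serves the item under Secondary objectives on whether treatment proposed with the DSS is more effective than treatment proposed without it.

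The tests follow in the same section. After a Kolmogorov-Smirnov check, the rule for numeric data is "If normality is met, Student’s *t* test will be used" and "If not, a non-parametric Mann-Whitney *U* test will be used instead". No outcome is named for this rule. The next sentence does name outcomes: "For comparisons before and after treatment, a paired *t* test will be used regarding numeric data", with questionnaire scores as its example and a normality check beforehand. The threshold is given as "Statistical significance will be set to 0.05", without saying whether tests are one- or two-sided.

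No baseline-adjusted model appears in the article.

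**The concern.** The stated question and the test attached to it do not match. The question is whether improvement differs between randomised groups. A paired t test asks whether the mean change within one set of patients differs from zero. Run once per arm, it gives two p-values, neither of which tests the difference between arms. One arm can cross 0.05 and the other miss it with no true difference, and both can cross it when one arm does much better.

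This is a matter of a test being named that does not fit the comparison, so it is more than detail left to a later document. At stake is the article's only patient-reported comparison of treatment effect. An analyst who follows the sentence on questionnaire scores literally would produce within-arm results and could present them as evidence for or against the DSS.

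A lesser part concerns precision. Baseline scores are collected, but no test named in the article uses them as a covariate.

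**Working it through.** **Nothing to reproduce.** The article gives no SD, expected change, correlation or power for these scores, and Sample size says that 200 was not formally calculated. The figures below are illustrations under stated assumptions.

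**Inputs from the article**
- Alpha 0.05 (Statistical analysis); two-sided is assumed.
- "Eligible patients will be randomised in a 1:1 ratio (100 participants in each group" (Sequence generation), so n = 100 per arm if all patients are analysed.
- 50 patients per country (Sample size), with Part II run only in the United Kingdom and Greece (Schedule of intervention). If the analysis were limited to Part II countries, 2 × 50 = 100 patients, about n = 50 per arm.

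**Assumed inputs**
- Correlation r between baseline and three-month score: 0.3, 0.5, 0.7.
- Common true improvement g in both arms: 0.2, 0.3, 0.5 SD of the score.
- No true difference between arms.

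**Step 1: paired tests read side by side.** The SD of change is √(2(1 − r)) in score SDs. The non-centrality is g√n / √(2(1 − r)) on n − 1 degrees of freedom, and p is the chance that one arm is significant. The arms contain different patients, so the chance that exactly one is significant is 2p(1 − p).

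Worked case, r = 0.5 (SD of change = 1), g = 0.3:
- n = 50: non-centrality 0.3 × √50 = 2.12; p = 0.548; 2 × 0.548 × 0.452 = 0.495.
- n = 100: non-centrality 0.3 × √100 = 3.0; p = 0.844; 2 × 0.844 × 0.156 = 0.263.

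Chance that exactly one arm is significant:

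| n per arm | r | g = 0.2 | g = 0.3 | g = 0.5 |
|---|---|---|---|---|
| 50 | 0.3 | 0.339 | 0.487 | 0.277 |
| 50 | 0.5 | 0.406 | 0.495 | 0.123 |
| 50 | 0.7 | 0.491 | 0.359 | 0.012 |
| 100 | 0.3 | 0.475 | 0.413 | 0.026 |
| 100 | 0.5 | 0.500 | 0.263 | 0.003 |
| 100 | 0.7 | 0.399 | 0.059 | 0.000 |

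The range is about 1% to 49% at 50 per arm and about 0% to 50% at 100 per arm. A simulation of the case n = 50, r = 0.5, g = 0.3 (20,000 replicates) gave 48.7% discordant results. A two-sample t test on change scores rejected in 5.1% of the same simulated trials, close to the nominal level.

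**Step 2: what baseline adjustment adds.** In units of the score variance, a change score has variance 2(1 − r), and ANCOVA has residual variance 1 − r². The ratio is (1 − r²) / (2(1 − r)) = (1 + r)/2.

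| r | change score | ANCOVA | ratio | power, change-score t | power, ANCOVA |
|---|---|---|---|---|---|
| 0.3 | 1.40 | 0.91 | 0.65 | 0.561 | 0.746 |
| 0.5 | 1.00 | 0.75 | 0.75 | 0.705 | 0.823 |
| 0.7 | 0.60 | 0.51 | 0.85 | 0.898 | 0.938 |

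The power columns assume 50 per arm and a between-arm difference of 0.5 SD.

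**The case against.** The strongest reply is that a between-arm test is named. Mann-Whitney is a two-sample test, so the Student's t / Mann-Whitney pair is plainly a rule for comparing groups, and the listed comparison is of groups. On that reading the arms are compared by a two-sample test of change, and the paired test only describes change over time. The text allows this, so a reader who infers that the trial will certainly rest its claim on two within-arm p-values goes too far: nothing says that the paired test replaces the arm contrast or that the two results will be set against each other. What remains is that the general rule names no outcome, while the next sentence gives questionnaire scores a test of their own.

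Three further points have force.
- A two-sample t test on change scores would be valid. ANCOVA is a gain in precision and protection against chance baseline imbalance, and does not repair an invalid test.
- A reader might take 50% as the expected rate of misleading results. It is the ceiling of 2p(1 − p), reached only when p is near one half. If both arms improve substantially, both will be significant and discordance is rare, as the g = 0.5 column shows.
- A reader might infer that at most 100 patients will be analysed. Part II is limited to two countries, but the Part II and Follow-up sections have every patient reviewed at three months, so the number is not settled.

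**Conclusion.** The point holds in limited form. The article poses a between-arm question for the DHI, EQ-5D-3L and VAS, and the only test it ties to questionnaire scores is a paired one that does not compare arms. The general two-sample rule may have been meant to cover the contrast, but the text leaves that open.

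Should the paired tests be used to judge the DSS, the chance of exactly one significant arm under equal improvement is uncontrolled: about 0% to 50% over the assumed values. Replacing a change-score t test by ANCOVA would reduce the variance to between 0.65 and 0.85 of its value, for assumed correlations of 0.3 to 0.7. These figures also take equal variance at both visits, two-sided testing and independent patients.

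The correction should be made, but its reach is modest: it concerns a secondary objective in a feasibility trial and does not touch the primary outcome of agreement with the overseeing expert.

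**What to change.** For each of the three scores, state that the inferential analysis is a between-arm ANCOVA: three-month value as outcome, with arm, baseline value and country or centre as covariates. Centre belongs in the model because, under Sequence generation, the randomisation lists are made per centre. Report the adjusted mean difference with a 95% confidence interval, and use robust or bootstrap standard errors if residuals are skewed. Keep paired within-arm changes as description only, with no inference about the DSS drawn from them. State which patients enter this analysis.

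A random effect for doctor or therapist is optional. With at most six patients expected per doctor, it may be poorly estimated.

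The cost is a few sentences in the analysis text. The baseline scores are already planned, so no new data are needed.
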